## Methods

### Study design

This is an RCT (Fig. 2) with a 9-month intervention and a 3-month follow-up. This program will consist of two arms: the intervention group (BCW-based interactive pictorial health education program) and the control group (routine community lecture health education). Prior to the trial, we completed the final draft of the BCW-based interactive pictorial health education program through medical staff and patient interviews and the Delphi method. A pre-experiment was conducted to assess the acceptability and feasibility of the intervention and research procedures in hypertensive patients with low health literacy in Huzhou, Zhejiang, China. We obtained informed consent from each study participant. The results of the two studies have been used to inform the development of the forthcoming trial.

**Fig. 2 Fig2:**
[figure not shown]
Overview of the study procedure

### Setting

The participants will be recruited from the community settings in Huzhou, Zhejiang Province, China. First, one of the municipal districts in Huzhou will be randomly selected, and then two communities with similar conditions within the district will be screened and selected. Finally, the two communities will be randomly allocated to the intervention group and the control group. Subjects meeting the inclusion criteria will be enrolled into the intervention group and the control group after informed consent is obtained. In addition, we will contact community health providers to participate in the study to ensure the cooperation of participants**.**

### Recruitment and study population

Our researchers will give out recruitment leaflets in the two selected communities. Health care providers in each community will also help introduce eligible individuals to our study. Three trained researchers will participate in an in-person interview to screen individuals who show interest for eligibility. All participants will be fully informed of the study protocol first and will only be included in this study upon signing informed consent before baseline measurements are taken. They will receive a gift for the completion of each session and each data collection stage. In addition, those who have a severe mental disorder or cognitive impairment at present, or who experience adverse events during the intervention or follow-up period will be withdrawn from the study. Detailed inclusion and exclusion criteria are as follows.

Inclusion criteria:Aged ≥ 18 years and have lived in Huzhou for at least half a yearDiagnosed as hypertensive according to the 2018 Chinese Guidelines for the Prevention and Treatment of Hypertension, systolic blood pressure (SBP) ≥ 140 mmHg and/or diastolic blood pressure (DBP) ≥ 90 mmHgChinese High Blood Pressure-Health Literacy Scale (C-HBP-HL) score < 40 pointsNo major stress events (e.g., the death of relatives) within the past 6 monthsAble to communicate in Mandarin, voluntarily participating in the study, and signing the informed consent of research intentionAt least one modifiable cardiovascular risk factor

Exclusion criteria:Any individuals with secondary hypertensionSevere mental disorder or cognitive impairment

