**Fig. 1 Fig1:**
[figure not shown]
The behavior change wheel consists of three layers. The center layer is composed of the Capability, Opportunity, and Motivation model. The second layer is composed of nine intervention functions which are the general methods by which interventions might change behavior. Examples are “education” and “persuasion.” The topmost layer of the wheel itemizes the policy categories that can be used to support the implement of these functions

To address this problem, we intend to develop an interactive pictorial health education program based on the nine intervention functions of BCW theory, which is targeted to improve the health literacy and self-management capacity for hypertensive patients with low health literacy.

Our study attempts to answer two primary questions:(i)Is it feasible to use the interactive pictorial health education program based on BCW theory for application in the community setting? We hypothesize that hypertensive patients with low health literacy would be willing to participate in this program and would have high compliance, and there would be no adverse events occurring during the intervention.(ii)What are the impacts of interactive pictorial health education programs based on BCW theory on hypertensive patients with low health literacy? We hypothesize that participants receiving BCW-based interactive pictorial health education program interventions compared with a routine community lecture health education only group will demonstrate an improvement in HBP-HL, HRQOL, self-management ability, and self-efficacy and a reduction in blood pressure.

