### Randomization and blinding

#### Sequence generation

After completing the screening of the two communities with similar size, educational background and economic income, randomization will be performed at the level of the community after recruitment is completed. One community will be randomized to receive the intervention, and the other community will be randomized to the control group by throwing dice. The randomization process will be completed by a third party unrelated to the study. Only after the subjects have completed the baseline data collection, the allocation personnel can inform the researchers of the allocation results.

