#### Allocation concealment

Participants and the trial coordinator will not be blinded to their group allocation; however, the data collectors and the data analyst will be blinded. The codes will be broken following statistical analysis.

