#### Feasibility

We will calculate the proportion of participants completing the intervention. Attendance will be examined as the proportion of participants who attend 9/11 sessions and the average number of sessions attended. At the end of each intervention session, a 5-point Likert scale (not at all to very much) will be used to rate all participants to gauge their level of satisfaction with the project and their mental and social engagement. At the 3-month follow-up assessment, participants will indicate their level of interest in participating in the project in the future and whether they would recommend it to others.

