### Dropouts and missing data

Reasons for dropouts will be documented and reported. If patients are alive and missing at random, we will use multiple imputation methods based on ten imputed datasets with multiple imputation by chained equations [37].

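### Withdrawing every participant who has an adverse event, with no stated outcome collection afterwards, can bias the comparison and cuts short event follow-up

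*Protocol article*

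**What the plan says.** Recruitment and study population: participants "who experience adverse events during the intervention or follow-up period will be withdrawn from the study". The consequence is withdrawal from the study, not from the sessions. No seriousness or relatedness threshold is attached, and the article does not say that outcomes are measured after such a withdrawal.

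Five other places bear on this rule:

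- Sequence generation: "randomization will be performed at the level of the community after recruitment is completed". The period covered by the rule therefore comes after allocation.
- Allocation concealment: "Participants and the trial coordinator will not be blinded to their group allocation".
- Primary questions, end of Background: the feasibility hypothesis expects high compliance and that "there would be no adverse events occurring during the intervention".
- Feasibility: "We will calculate the proportion of participants completing the intervention". The section also uses attendance and questions put to participants at the 3-month follow-up.
- Dropouts and missing data: "Reasons for dropouts will be documented and reported", and then "If patients are alive and missing at random, we will use multiple imputation methods based on ten imputed datasets".

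**The concern.** The rule removes people because of something that happens after allocation. The outcomes include blood pressure, quality of life and self-management, and an adverse event in a hypertensive adult is plausibly related to all three. A link to the primary outcome is also plausible, since the Background cites evidence that people with low health literacy have more adverse health outcomes than those with high literacy. If such people leave at different rates in the two arms, or differ from those who stay by different amounts, the remaining groups are no longer comparable in the way the allocated groups were.

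Differential removal is a realistic risk. Participants and coordinator know the allocation. The intervention content (Table 1) teaches people to recognise complications, monitor blood pressure and communicate with medical staff, which could change how often events are reported in that arm.

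The feasibility question is affected as well. A withdrawn participant becomes a non-completer because of the rule, whatever their willingness to continue, and would not be asked the closing questions on interest and recommendation. Later events and the course of the first event go unobserved.

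**Working it through.** **1. The plan's own figure.** The only stated number that the rule touches is the enrolment target. Sample size calculation gives 108 before dropout and a 10% allowance: 108 / (1 − 0.10) = 120, which reproduces. The allowance is 120 − 108 = 12 people. The 108 is taken as stated, because this point does not depend on how it was derived.

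**2. Numbers left.** The article gives no adverse-event rate, so the rates here are assumptions. If event withdrawals come on top of the 10% dropout, the number left is 120 × 0.90 × (1 − a), and the enrolment needed to keep 108 is 108 / (0.90 × (1 − a)), rounded up.

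| Assumed event rate a | Left of 120 | Enrolment needed for 108 |
|---|---|---|
| 0% | 108 | 120 |
| 2% | 105.8 | 123 |
| 5% | 102.6 | 127 |
| 10% | 97.2 | 134 |
| 20% | 86.4 | 150 |

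If event withdrawals are already inside the 10%, there is no extra shortfall until the 12 are used up.

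**3. Complete-case bias in the health-literacy score.** The pilot means and SDs are 32.09 ± 4.89 and 27.80 ± 4.78. The difference is 32.09 − 27.80 = 4.29 points. The pooled SD is √((4.89² + 4.78²)/2) = 4.835.

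Let a be the share of an arm withdrawn for events, and δ the amount, in SD, by which those people would have scored below the rest. The mean of those who remain then exceeds the mean of the whole arm by a × δ × SD. With I for intervention and C for control:

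bias = (a_I δ_I − a_C δ_C) × 4.835

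| a_I vs a_C (assumed) | δ, both arms (assumed) | Bias, points | Share of 4.29 |
|---|---|---|---|
| equal | equal | 0 | 0% |
| 10% vs 5% | 0.5 | 0.05 × 0.5 × 4.835 = 0.12 | 3% |
| 10% vs 0% | 1 | 0.10 × 1 × 4.835 = 0.48 | 11% |
| 20% vs 5% | 1 | 0.15 × 1 × 4.835 = 0.73 | 17% |

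The sign reverses if the control arm loses more. Equal rates alone do not guarantee zero: 10% in both arms with deficits of 1 and 0.5 SD gives 0.10 × 0.5 × 4.835 = 0.24 points. The table is illustrative and not a bound: 20% against 0% at 1 SD would give 0.20 × 4.835 = 0.97 points. For blood pressure and quality of life the article gives no SDs, so the bias there cannot be sized.

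**4. Whether the planned imputation removes it.** Imputation is conditional on data being missing at random. Under the rule, everyone with an event leaves in both arms, so no outcome after an event is observed in anyone. Baseline values, and the 6- or 9-month values where already taken, can enter the model. The relation between having had an event and later outcomes cannot be estimated, because the model would learn only from event-free follow-up.

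**The case against.** The strongest reply has four parts.

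- **The safety hypothesis.** A reader might infer that the rule defeats it, because those with events leave the data. The article does not support that. Reasons for dropout are documented and reported, so a first event remains countable and can by itself refute the expectation of no events. Nor does withdrawal mean that data already collected are deleted. What is lost is later events and the course of the first.
- **Feasibility.** A reader might also infer that it is assessed only in those who stay well. On its natural reading, the completion proportion keeps withdrawn people in the denominator as non-completers. The rule can lower that figure; it does not restrict it to survivors.
- **Bias.** It is possible, not shown. It is zero when rates and deficits are equal across arms, every rate and deficit above is assumed, and the calculation ignores imputation. Missing at random is conditional on observed data, and nothing in the article proves it false or excludes these withdrawals from imputation. If they are imputed, the groups can still be analysed as allocated.
- **Condensed article.** The definition of an adverse event and the procedural detail of withdrawal may stand in the full protocol. The 10% allowance may also be meant to cover these losses.

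All of this stands as a limit on how strongly the point may be put. It does not remove the point. The rule itself is stated, its trigger is post-allocation, and an analysis plan cannot recover outcomes that the protocol stops collecting.

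**Conclusion.** The point holds in a limited form. The rule can bias the between-group comparison, weakens the feasibility measures and truncates adverse-event follow-up. It does not necessarily bias the comparison, and it does not make the no-events hypothesis untestable.

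The size cannot be fixed from the article. Across the tabulated scenarios, complete-case bias in the primary score is 0 to 0.73 points, or 0–17% of the pilot difference. That would distort an effect of the pilot's size without reversing it. Any shortfall below 108 depends on event withdrawals exceeding the 10% allowance. Both calculations rest on assumed event rates; the bias also assumes that people with events would have scored lower. The imputation criticism rests on the text alone: its condition is doubtful for these losses, and no post-event data would exist to inform it.

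**What to change.** Reconcile the primary questions, Recruitment and study population, Feasibility, and Dropouts and missing data so that an adverse event does not end outcome data collection. Specifically:

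- Collect the 6-, 9- and 12-month outcomes (T1–T3) from everyone who has not withdrawn consent, including those who have had an event.
- Analyse all participants in the group to which their community was allocated.
- Report adverse events by arm as part of feasibility.

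Whether a participant continues the sessions after an event is a clinical matter and is not addressed here.

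The cost is a wording amendment, by the route the article gives (agreement of the Supervising Committee and ethics approval), and a few extra outcome visits or calls.

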### Randomization and blinding

#### Sequence generation

After completing the screening of the two communities with similar size, educational background and economic income, randomization will be performed at the level of the community after recruitment is completed. One community will be randomized to receive the intervention, and the other community will be randomized to the control group by throwing dice. The randomization process will be completed by a third party unrelated to the study. Only after the subjects have completed the baseline data collection, the allocation personnel can inform the researchers of the allocation results.

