## Strengths and limitations of this study

The main strength of the study lies in establishing a new health management program for hypertensive patients combining BCW theory and HBP-HL closely to better address the problem under study.Further strengths are that we will match the intervention and control cases in order to reduce bias and confounding factors as much as possible as well as the fact that data are collected in a naturalistic situation.One limitation is that the trial is not double-blinded and will be implemented in only two communities.Another possible limitation of this study is the short 9-month intervention and 3-month follow-up intervention, which may not be long enough to observe the effect of the intervention on the occurrence of hypertension complications.

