#### Sample size calculation

The Gpower3.1.9.2 software was used to conduct the sample size calculation. The sample size was estimated by power analysis using the Chinese high blood pressure-health literacy scale for the evaluation of HBP-HL as a primary outcome measure of the study. Cohen’s *d* and the effect sizes were calculated for between-group differences of means of the level of HBP-HL using an independent-groups pre-test and post-test design. From the evidence of our pilot study, the HBP-HL score of the intervention group was 32.09 ± 4.89 points, and that of the control group was 27.80 ± 4.78 points, which led to an estimate effect size as 0.405. The analysis, with a two-sided test using *β* = 0.2, *α* = 0.05, two sample *t-test*, and repeated ANOVA, requires a total sample size of 108 participants. Considering a 10% dropout rate, our final sample size comes to 120 participants (60 participants for both the intervention and control groups).

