#### Intervention

Participants in each group will be divided into 3 teams of 15–20 people. Intensive intervention will be carried out for 9 months and twice a month in the first 2 months. During the other months, the intervention will be conducted once a month. Later, 3 months of follow-up will be conducted over telephone once a month and hypertension-related knowledge and videos (Putonghua and Huzhou dialect version) will be sent to the WeChat group once a week. Intermediary data will be collected at the 6th and 9th months to obtain timely feedback, to correct deviations, and to monitor and ensure the successful implementation of the intervention.

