### Statistical analysis

The SPSS 23.0 software will be used for data processing and statistical analysis. Descriptive statistics will be used to process sociodemographic data, of which observable variables are presented as the means ± standard deviations for continuous variables and frequencies and percentages for categorical variables. Exploratory analysis will be applied to examine the distribution of data. Baseline data comparisons between the two groups will be conducted using the chi–square (*χ*^2^) test (for categorical variables) and *t-test* or Wilcoxon rank-sum test (for continuous variables). 2(group)× 3(time) ANOVA is used for data with a normal distribution and homogeneity of variance, and a generalized estimation equation is used for data with a nonnormal distribution to determine the main effect of intervention factors, time factors, and interaction between group factors and time factors. Simple effects will be further analyzed when there are interaction effects. A two-tailed *P* < 0.05 will be considered statistically significant.

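### With one community per arm, the arm effect cannot be separated from the community, and the patient-level P values test the program only if between-community variance is zero

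*Protocol article*

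**What the plan says.** - **Allocation.** Under Sequence generation, "randomization will be performed at the level of the community after recruitment is completed", and then "One community will be randomized to receive the intervention, and the other community will be randomized to the control group by throwing dice". The Setting section agrees: two similar communities in one district, one for each group.
- **Label.** The Study design section states "This is an RCT (Fig. 2) with a 9-month intervention and a 3-month follow-up". The Abstract also calls it a randomized controlled trial. Neither place calls it a cluster trial.
- **Sample size.** The calculation assumes independent groups, "with a two-sided test using *β* = 0.2, *α* = 0.05, two sample *t-test*, and repeated ANOVA". It arrives at 108 patients, raised to 120 (60 per group) for 10% dropout. No ICC or design effect appears.
- **Analysis.** The Statistical analysis section plans a 2 (group) by 3 (time) ANOVA, or a GEE for non-normal data, "to determine the main effect of intervention factors, time factors, and interaction between group factors and time factors", judged at two-tailed P < 0.05. Community is neither a model term nor named as a clustering level.
- **Limitation.** The Strengths and limitations section lists the use of only two communities as a limitation. It draws no consequence for the analysis or the conclusion.
- **Intended conclusion.** The Background and Discussion state efficacy hypotheses. The end of the Discussion foresees offering a validated program to community providers if the project succeeds.

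**The concern.** Everyone in one community receives the program and everyone in the other receives routine lectures. Whatever else makes the outcomes of the two communities diverge over 12 months, such as local providers or concurrent health activities, goes into the same contrast as the program. The patient-level standard error contains only variation between patients within a community, so it treats the between-community part as zero.

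At stake is the main claim. A significant group effect or interaction would be reported as randomised evidence that the program raises health literacy, when the design has a single replicate of each condition. The feasibility question is largely untouched.

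**Working it through.** **1. The plan's own figures.** The dropout step reproduces: 108 / 0.9 = 120. The 108 itself does not follow from the stated inputs. The control pilot score is 27.80 ± 4.78, and "the HBP-HL score of the intervention group was 32.09 ± 4.89 points". The pooled SD is √((4.89² + 4.78²)/2) = 4.835, so d = 4.29/4.835 = 0.887. The stated 0.405 matches the correlation form d/√(d² + 4) = 0.4055. That is a separate matter, and nothing below depends on it. I use 108/2 = 54 evaluable patients per arm, which is also 54 per community.

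**2. Degrees of freedom.** Two communities minus two arm means leaves 2 − 2 = 0 degrees of freedom between communities. A randomisation test has 2 possible allocations, so its smallest P value is 0.5 one-sided and 1.0 two-sided. A GEE clustered on community would have one cluster per arm and no usable robust variance.

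**3. Size under assumed ICCs.** The documents give no ICC, so the values below are assumptions. They refer to whatever is compared: a score at one time point, or a change score. With m = 54:

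- design effect DE = 1 + (m − 1) × ICC
- standard error multiplier = √DE
- real two-sided error = 2 × (1 − Φ(1.96/√DE))

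| Assumed ICC | DE | √DE | 1.96/√DE | Real error |
|---|---|---|---|---|
| 0 | 1.000 | 1.00 | 1.96 | 5.0% |
| 0.001 | 1.053 | 1.03 | 1.91 | 5.6% |
| 0.005 | 1.265 | 1.12 | 1.74 | 8.1% |
| 0.01 | 1.530 | 1.24 | 1.58 | 11% |
| 0.02 | 2.060 | 1.44 | 1.37 | 17% |
| 0.05 | 3.650 | 1.91 | 1.03 | 30% |

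**4. Check.** The planned test estimates its variance within communities. Allowing for this, the t statistic is inflated by √(1 + m × ICC/(1 − ICC)). For m = 54 this gives 5.6%, 8.2%, 11.4%, 17.4% and 31.4% for the five non-zero ICCs, so the simple formula is slightly conservative. With 60 per community the same calculation gives 12.1% at ICC 0.01 and 33.4% at 0.05; simulation (20,000 runs) gave 12.0% and 33.6%.

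**5. In scale points.** With the pilot SD, the patient-level standard error of a difference is 4.835 × √(2/54) = 0.93 points. At ICC 0.05 it becomes 0.93 × 1.91 = 1.78 points.

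**6. What the interaction does.** A community difference that is the same at every time in the model cancels from the group-by-time term. It stays in the group main effect, which the plan also tests. A difference in change over time between the communities stays in both.

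**The case against.** The design has real safeguards. The two communities lie in one district and are chosen for similar size, education and income. A third party performs the allocation, which is released only after baseline. Community allocation is described openly, and the restriction to two communities is admitted. The small ICCs in the table may therefore be the relevant ones, and at 0.001 the error is barely raised. All of this stands, but it reduces imbalance and selection without supplying replication, and two communities cannot show which ICC applies. Nor can this be left to a statistical analysis plan: the allocation unit is fixed here, and no model separates two identical variables.

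Some stronger readings are tempting but unsupported:

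- A reader might infer that the P values mean nothing, or that every difference between the communities is counted as program effect. They do describe the difference between these two sets of patients, and the interaction removes time-constant differences.
- A reader might infer that the outcomes are compared by t-test. The Statistical analysis section uses it for baseline comparisons only; otherwise it appears in the power calculation.
- The plan says "Participants in each group will be divided into 3 teams of 15–20 people". A reader might infer discussion-driven team clustering in both arms. The map-guided discussion belongs to the intervention group; controls receive lectures.
- From "we will match the intervention and control cases in order to reduce bias and confounding factors as much as possible" a reader might infer a promised patient-level matching that is never carried out. The remark can equally mean the selection of similar communities.

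**Conclusion.** The point holds. Allocation is by community with one per arm, while sizing and testing are by patient. As tests of the program, the planned P values rest on zero between-community variance, an assumption that the article does not state and that its data cannot check. More patients from the same two communities would not help.

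The structural conclusion needs no assumed figure. The error rates, about 5.6% to 30% against a nominal 5%, do: they rest on ICCs of 0.001 to 0.05, 54 patients per arm, and a single-time-point or change-score comparison. They are not the exact error of the full 2 by 3 interaction test. The single sentence on two communities under Strengths and limitations does not repair this, because the test, the power statement and the intended conclusion remain as they are.

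**What to change.** 1. **Abstract and Study design:** describe the study as a cluster-allocated comparison of two communities, one per arm.
2. **Background (study questions), Statistical analysis and Discussion:** replace the P < 0.05 efficacy test, and the language that anticipates a proven and validated program, with an estimate and interval for the difference in change between these two communities. State that it does not separate program from community. Keep feasibility as a full aim.
3. **Sample size calculation:** state that the 80% power assumes a community ICC of zero.
4. **Statistical analysis:** add a sensitivity table that multiplies the standard error by √(1 + (m − 1) × ICC) for assumed ICCs of 0, 0.005, 0.01, 0.02 and 0.05. With m = 54 the multipliers are 1.00, 1.12, 1.24, 1.44 and 1.91. The interval widens; the estimate does not change.
5. **Optional:** a random effect for team, as a secondary sensitivity analysis only, with a statement that it does not correct for community. With six teams nested in two communities, it could otherwise make the interval look corrected when it is not.

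The cost is a less favourable claim and wider intervals. The changes are to wording plus one table, with no extra patients.
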